### Materials

#### Interventions

**Psychotherapy Trauma-Focused Cognitive Behavioral Therapy (TF-CBT)** Participants allocated to the TF-CBT intervention, will receive 12 weekly sessions with a certified therapist who strictly follows a clinician manual for TF-CBT. CBT will be given by therapists who have clinical experience and at least a Master’s degree in Clinical Psychology or in Medicine and should have followed the training for TF-CBT at our department, in order to properly execute the clinician manual. The therapist will receive supervision regularly (once a month) and all sessions will be tape-recorded.

Trauma-Focused Cognitive Behavioral Therapy (TF-CBT) will be based on the model originally developed by Foa for female victims of rape [40]. In TF-CBT exposure (both in vivo and imaginal exposure) and cognitive restructuring (examining and challenging dysfunctional thoughts) are the most prominent elements next to psycho-education and anxiety management (e.g. muscle relaxation or breathing retraining). Subjects will take part in a structured therapy that follows a strict protocol developed by Creamer et al. [41] and based on the assumption that mental health specialists should be well-trained in the use of exposure, and particularly imaginal exposure. The clinician manual of Creamer is further developed and adjusted by the research staff of the current study. The first sessions are devoted to establishing a therapeutic alliance, giving psycho-education, and teaching relaxation skills and will take 60 minutes. Anxiety management strategies may be introduced, which include physical (i.e. breathing control, relaxation techniques, aerobic exercise, reducing stimulants such as caffeine and nicotine), cognitive (i.e. thought stopping, distraction techniques, imagery) and behavioral interventions (for addressing other associated problems, such as sleep disturbance, assertion and communication deficits). Not all strategies need to be provided, but according to the specific client several can be selected. In addition, the theoretical rationale of exposure-based therapy is introduced and repeated throughout treatment. Furthermore, the principle of the Subjective Units of Distress Score (SUDS), a rating system on a 100-point scale ranging from 0 (no anxiety) to 100 (extreme anxiety), is introduced and targets for exposure are identified. The following sessions imaginal exposure will be done. During imaginal exposure, the patient retells the traumatic experience in detail, SUDS are being registered and “hot spots” identified until anxiety reduction occurs. Exposure sessions can be accompanied by cognitive restructuring and focus on identifying, challenging and replacing maladaptive thought and beliefs associated with the trauma. The number of exposure sessions depends on the severity of the distress and the decrease of anxiety and will be 90 minutes. Homework assignments include practicing muscle relaxation or breathing techniques, confronting feared but safe situations (in vivo exposure), and daily listening to a taped narrative of the trauma (imaginal exposure). At the final sessions treatment progress is evaluated and relapse prevention is provided, reviewing the techniques used in therapy, evaluating their helpfulness, and discussing general termination issues. The relapse prevention session will be 60 minutes.

Each session, the therapist documents mental health status with the Clinical Global Impression scale. All subjects will be asked to weekly fill out the Impact of Event Scale-Revised [42].

##### Pharmacotherapy paroxetine (Seroxat)

Participants allocated to the pharmacotherapy intervention will receive paroxetine (Seroxat). Treatment will be given by certified psychiatrists according to a manual that is developed and adjusted by the research staff of this study.

Pharmacotherapy will be in accordance with Dutch guidelines of pharmacotherapy for anxiety disorders [8] and the NICE guidelines for clinical excellence [9]. Paroxetine treatment will start with psycho-education and discuss paroxetine intake and possible side effects. Paroxetine treatment will be initiated at 20 mg daily for 4 weeks. After 4 weeks the study psychiatrist can increase the dosage with increments of 10 mg daily each 4 weeks up to a maximum of 60 mg daily if according to the judgement of the study psychiatrist, the patient does not respond to lower dosages and if clinically tolerated. After 24 weeks of treatment the antidepressant will be gradually discontinued (tapering off in 10 or 20 mg decrements per week). If discontinuation/withdrawal symptoms do emerge and are mild, the psychiatrist will reassure the patient that these symptoms are not uncommon after discontinuing an antidepressant and will disappear in a few days. If symptoms are severe, reintroduction of the original antidepressant and gradual tapering is required.

On each visit during treatment the psychiatrist monitors for adverse side effects, evaluates compliance with the Morisky Medication Adherence Scale [43] and documents mental health status with the Clinical Global Impression scale. All subjects will be asked to fill out the Impact of Event Scale-Revised [42]. Every session takes 20–30 minutes. The psychiatrist will be instructed not to perform any direct psychotherapeutic interventions at the visits.

### Assessments

Assessments will take place pre-intervention (T0), 1 week post-intervention (T1) and 3, 6, 12 and 18 months at follow-up (T2-T5). Below we will describe the instruments that we will use in more detail.

### Clinical assessments

*Clinician Administered PTSD Scale (CAPS)* is one of the most widely used structured clinical interviews for diagnosing PTSD according to DSM-IV [44] and assessing PTSD symptom severity [37]. The CAPS distinguishes between the estimated frequency (range: 0–4) and intensity (range: 0–4) of the various symptoms. Frequency and intensity scores are added up to a total CAPS score (range: 0–136). The Dutch translation of the CAPS exhibits adequate validity and reliability. The internal consistency of this scale is good with alpha .63 for re-experiencing, .78 for avoiding and .79 for hyperarousal and .89 for all core PTSD symptoms together [45].

*Clinical Global Impression scale (CGI)* will be used to assess the response rate by rating the proportion of responders with a CGI improvement rating of “very much improved” or “much improved”. The CGI was first developed for use in psychopharmacology trials as part of the NIMH collaborative study of schizophrenia [46]. Since then it has been used as a standard primary outcome measure in studies investigating the efficacy of pharmacological treatments. Criteria for response will be a 30% or greater change from baseline on the CAPS and a final CGI rating of 1 or 2 (“much improved” or “very much improved”).

*M.I.N.I. International Neuropsychiatric Interview-Plus (M.I.N.I.-Plus)* will be used to assess psychopathology [47]. The M.I.N.I.-Plus is a widely used structured clinical interview that can diagnose past and present DSM-IV psychiatric disorders, such as mood disorders (i.e. major depressive, dysthymic or manic disorder), anxiety disorder (i.e. panic disorder, generalized anxiety disorder or obsessive compulsive disorder) or substance related disorders. Every module consists of screening questions which, if responded positively, will lead to additional examination for diagnosing the specific disorder. The M.I.N.I-Plus has reasonable to good interrater reliability (i.e. .84 for major depressive disorder and .43 for drug dependence). A Dutch translation of the M.I.N.I.-Plus is available [48].

### Self-report assessments

*Basic demographic variables*, i.e. birth date, sex, marital status, number of children, origin of parents, highest level of education, profession, number of working hours will be assessed.

*Trimbos/iMTA questionnaire for Costs associated with Psychiatric Illness (TiC-P)* is used to document resource utilization to estimate direct (i.e. medical consumption) and indirect costs (e.g. work absenteeism) associated with psychiatric illness [49]. Volumes of resource utilization will be valued by unit costs estimated according to the Dutch guideline on (unit) costing in healthcare [50]. GP visits, medical specialist visits, physical therapists, and travelling will be valued based on the guideline prices. Psychotherapy sessions will be based on reported expenses or recommended prices from the professional associations. Medication costs will be valued by their market prices [51]. The friction cost method will be used to estimate the duration of lost productivity, age adjusted average daily wages will be used to value this duration.

*World Health Organization-Quality of Life Bref (WHOQOL)* assesses quality of life [52]. The WHOQOL is a 26-item questionnaire to measure quality of life, including physical health, psychological health, social relationships and environment. Items are scored on 5-point scales from 1 (worse outcome) to 5 (best outcome) with a total range from 4–20. The Dutch version has demonstrated good content validity, construct validity and reliability [53].

*Euroqol 6-Dimensions scale (EQ-6D)* is an easy to apply self-administered questionnaire for describing and valuing quality of life [54] and can be used to generate cross-national comparisons of health state. The first part measures five health dimensions: mobility (MO), self-care (SC), daily activities (DA), pain/discomfort (PD), mood (MD) consisting of both anxiety and depression and cognitions (CD). In the EQ-6D patients report: 0 (no problems), 1 (moderate problems), and 2 (extreme problems). The second part (EQ-VAS) is a thermometer-like scale, in which patients rate their overall wellbeing from 0 (worst imaginable overall health) to 100 (best imaginable overall health). It originated from the ED-5D [55] that is shown to be valid and frequently used to assess generic quality of life and health status [56].

*Treatment preference* will be assessed by a question concerning of the preferred treatment if they would have had a choice. Preferred treatment can be indicated as: ‘TF-CBT’, ‘paroxetine’ or ‘no preference’.

*Hospital Anxiety and Depression Scale (HADS)* will be used to assess the level of depression and anxiety symptoms [57]. It is a well-established 14-item scale containing two subscales: HADS-A (Anxiety, 7 items, range: 0–21) and HADS-D (Depression, 7 items; range: 0–21). The HADS is validated in Dutch and showed satisfactory test-retest reliability for both subscale scores (Pearson’s r’s = .89 and .86 respectively) and validity [58].

*Life Events Checklist (LEC)* is a semi-structured interview that will be assessed to record the number and severity of the trauma(s) [59].

*Impact of Event Scale-Revised (IES-R)* is a questionnaire to assess the level of trauma reactions in the preceding 7 days that are associated with a traumatic event [42]. The IES-R contains 22 items (with 5-point Likert scales, 0–4) and three subscales, corresponding to the three symptom clusters in the DSM-IV PTSD diagnosis: re-experiencing (8 items, scale range 0–32), avoidance (8 items, range 0–32) and hyperarousal (6 items, range 0–24). The IES-R has been translated in Dutch and validated [60].

*Smoking screen* Standard Questionnaire Smoking (‘Standaardvraagstelling Roken’) is a questionnaire containing two questions that assess smoking habits. These questions have been used primarily by Dutch health organizations (GGD) to indicate smoking habits in elderly patients but are currently used to indicate smoking habits according to frequency and the variability (i.e. cigars, cigarettes) in other groups as well.

*Alcohol Use Disorders Identification Test (AUDIT)* was developed by the World Health Organization (WHO) in 1982 and is a screening instrument that assesses excessive drinking patterns and consists of 10 questions concerning recent alcohol use, alcohol dependence symptoms and alcohol-related problems [61]. This instrument is validated and designed for international use and cross-nationally standardized. The AUDIT identifies alcohol use as well as possible dependence, is brief, rapid and flexible and is consistent with the ICD-10 definitions of alcohol dependence and harmful alcohol use. Moreover, in several studies high validity as well as high reliability was found.

*Subjective Health Complaints Inventory (SHC)* is a 29-item scale that registers occurrence, intensity, and duration of subjective somatic and psychological complaints experienced during the past 30 days, without reference to specific diagnostic categories [62,63]. The intensity of each complaint graded on a 4-point scale (not at all/little/some/severe). An SHC total score is created by adding the scores of each item on somatic and psychological complaints. It records ailments based on objective diseases, but is particularly sensitive to health complaints with minimal or no clinical findings. The instrument can be divided into five categories: musculoskeletal pain, pseudo neurology, gastrointestinal problems, allergy and flu. The scores for each item range from 0 to 3, giving a total score from 0 (excellent) to 87 (very poor). The questionnaire has satisfactory validity and reliability.

*Morisky Medication Adherence Scale (MMAS)* is a self-reported measure of medication taking developed from a previously validated 4-item scale and supplemented with additional items addressing the circumstances surrounding adherence behavior [42].

### Procedure

All patients referred to the outpatient psychiatric clinic at the AMC will receive a diagnostic medical intake procedure, in which psychiatric and medical history are examined. In case PTSD diagnosis is suspected, the intake procedure will consist of standardized diagnostic measures for PTSD and other DSM-IV diagnoses (CAPS and M.I.N.I.-Plus). If PTSD is confirmed and all inclusion criteria are met, the patient will be requested to participate in the study. After giving informed consent, a baseline assessment (T0) will be performed. This assessment will consist of self-reported symptoms of PTSD, depression and anxiety and questionnaires on quality of life and costs. Subsequently, patients will be randomized to either TF-CBT or paroxetine treatment. One week after treatment, another assessment will be done (T1), consisting of the same questionnaires. At 3 months (T2), 6 months (T3), 12 months (T4) and 18 months (T5) assessments will be repeated. Figure 1 shows a flowchart of the study. Table 1 explores an overview on all instruments being assessed.

**Table 1 T1:** Overview of instruments per assessment time point

	***Baseline (T0)***	***Treatment***	***1-week follow-up (T1)***	***3-month follow-up (T2)***	***6-month follow-up (T3)***	***12-month follow-up (T4)***	***18-month follow-up (T5)***
**Instruments**							
*Clinical instruments*							
CAPS	X		X	X	X	X	X
CGI	X	X	X	X	X	X	X
M.I.N.I.- Plus	X		X	X	X	X	X
*Self-report instruments*							
TiC-P	X		X	X	X	X	X
WHOQOL	X		X	X	X	X	X
EQ-6D	X		X	X	X	X	X
Preference	X						
HADS	X		X	X	X	X	X
LEC	X		X	X	X	X	X
IES-R	X	X	X	X	X	X	X
Smoking Screen	X		X	X	X	X	X
AUDIT	X		X	X	X	X	X
SHC	X		X	X	X	X	X
MMAS		X					

*CAPS*: Clinician Administered Posttraumatic Stress Disorder Scale (Blake et al., 1995); *CGI*: Clinical Global Impression scale (Guy, 1976); *M.I.N.I*.-Plus: MINI International Neuropsychiatric Interview-Plus (Sheehan et al., 1998); *TiC-P*: Trimbos/iMTA questionnaire for Costs associated with Psychiatric illness (Hakkaart-Van Roijen et al., 2002); *WHOQOL*: World Health Organization Quality of Life (WHOQOL GROUP, 1998); *EQ-6D*: Euoqol 6-Dimensions (Hoeymans et al., 2005); *HADS*: Hospital Anxiety and Depression Scale (Zigmond & Snaith, 1983); *LEC*: Life of Events Checklist; *IES-R*: Impact of Event Scale-Revised (Weiss & Marmar, 1997); *AUDIT*: Alcohol Use Disorders Identification Test; *SHC*: Social Health Complaints Inventory (Ursin et al., 1988; Eriksen et al., 1999); *MMAS*: Morisky Medication Adherence Scale (Morisky et al., 2008).

### Statistical analyses

All analyses will be performed according to the intention-to-treat (ITT) principle. Patients will be classified as responders and non-responders to treatment. Criteria for treatment response will be a 30% or greater change from baseline on the CAPS and a final CGI rating of 1 or 2 (“much improved” or “very much improved”).

Patients will also be classified in terms of compliance with the treatment regime and completion of the treatment and study procedures. Completers are those patients who finished the study scheme and who were available for at least one post-intervention assessment. Compliance concerns the adherence of treatment protocol, i.e. taking medication. Non-compliant patients are those patients who failed to take their medications or who failed to adhere to the TF-CBT sessions for >25% of the time. Regarding drop-out and loss to follow-up, a careful procedure will be followed in order to avoid an early exclusion of non-completers. Furthermore, adequate methods for imputation of missing data will be used, such as Maximum Likelihood Estimation (MLE) or Multiple Imputation method (MI).

Descriptive statistics will be used to examine differences in demographic, trauma-related characteristics at baseline between the TF-CBT group and the paroxetine group. Continuous CAPS scores at post-intervention assessments will be compared using analysis of covariance with study treatment (SSRI or TF-CBT) as main effect, adjusting for differences at baseline and other potential confounders (i.e. gender, age). Differences between both treatment groups will be evaluated by analysis of repeated measures, using linear mixed models. In multivariate analyses we will adjust the estimated differences for potential confounding variables (i.e. gender, age, SES, co-existence of a moderate depression). Regarding drop-out and loss to follow-up, different analytical approaches (complete case analysis, last observation carried forward, multiple imputation, best/worst outcome) will be followed in order to assess their impact on the study results. All analyses will be performed using SPSS 18.0.

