### Research aims and hypotheses

The aim of the proposed study is to compare the effectiveness and cost-effectiveness of Trauma-Focused Cognitive Behavioral Therapy (TF-CBT) to paroxetine in patients with PTSD in a randomized controlled trial in terms of PTSD symptom reduction. Secondary outcome measures include general measures of psychological wellbeing (i.e. anxiety and depression), quality of life, and related costs. Furthermore, we will take into account treatment responses by gender, age, and socio-economic status (incl. ethnic and cultural background) as previous studies show that women are twice as likely as men to develop PTSD during their lifetime [2] and indicate that different psychobiological mechanisms may play a role in the development of PTSD in women compared to men [5].

Based on previous findings of the effects of both treatments on clinical symptomatology over time, we expect the TF-CBT treatment to be more effective in PTSD symptom reduction than paroxetine most prominently at long-term follow-up, i.e. several months or years after cessation of both treatments. Furthermore, we hypothesize that CBT will be cost-effective, especially related to less expected relapse rates in comparison with pharmacological treatment. We will take into account direct medical costs (health care utilization as well as to inpatient and outpatient mental health care, day-treatment and primary physician care), direct non-medical costs (travel to and from health care providers, out-of-pocket costs) and indirect costs (lost productivity due to sick leave).

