#### Sample size calculation adjustment

We decided to adjust the sample size calculation and to optimize the power of the trial given the current study design, resulting in a smaller but more feasible sample size, in the light of possible slow recruitment. The original sample size calculation was based on the outcome on a single follow-up measurement, and was therefore rather conservative. As repeated measurements during follow-up provide additional data, differences can be estimated with higher accuracy, and therefore a smaller sample size is required to demonstrate a similar difference.

The increase in power does not solely depend on the number of measurements, but also on the correlation between measurements on the same patient (intra class correlation or ICC). Additional measurements add relatively less information to previous measurements if measurements are highly correlated. The required sample size for our study was therefore based on the study of Rochon [39] showing that for five measurements on each patient, for ICCs from 0 to 0.5, between 36 and 68 patients are required in each arm with an effect size of Cohen’s *d*=0.3, while between 14 and 25 patients per arm are needed with an effect size of 0.5. With an anticipated effect size of 0.46 we would need between 20 and 36 (depending on the actual ICC) patients per measurement per arm, respectively to gain a difference of 12 points on the CAPS at 18 months post-treatment. Anticipating possible attrition of study participants of 20%, we aim for 45 patients in each arm for the entire study period. Our new sample size is in line with another comparative study on long-term treatment effects of SSRI versus trauma-focused psychological treatment up to date that indicates that a smaller sample size may be sufficient to demonstrate a difference at 6-month follow-up [11].

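### LOCF and an undefined best/worst rule are weak drop-out sensitivity analyses for a late-divergence hypothesis, and the listed set has no plausible missing-not-at-random check

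*Protocol article*

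**What the plan says.** The Statistical analyses section of the protocol article evaluates the treatment difference by "analysis of repeated measures, using linear mixed models". For missing data it says that "adequate methods for imputation of missing data will be used, such as Maximum Likelihood Estimation (MLE) or Multiple Imputation method (MI". Later in the same section it returns to drop-out and names four approaches, "complete case analysis, last observation carried forward, multiple imputation, best/worst outcome", which "will be followed in order to assess their impact on the study results". By that stated purpose the four are sensitivity analyses.

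Three other places bear on how these methods would behave:

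- Research aims and hypotheses: "we expect the TF-CBT treatment to be more effective in PTSD symptom reduction than paroxetine most prominently at long-term follow-up". The same section expects fewer relapses after CBT than after drug treatment.
- Assessments and Table 1: CAPS is taken at T0 and at T1 to T5 (1 week, then 3, 6, 12 and 18 months), with no CAPS in the treatment column. Participants sets a minimum CAPS of 45 for entry.
- Sample size calculation adjustment: "Anticipating possible attrition of study participants of 20%, we aim for 45 patients in each arm for the entire study period".

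**The concern.** The trial expects the arms to separate after treatment stops. A sensitivity analysis for drop-out should therefore ask what happens if the unseen late scores are worse than the observed data predict, possibly more so in one arm. LOCF does not ask this. It holds each lost patient at the last score seen. For a loss during treatment that is the untreated baseline score, and for a later loss it is a score that leaves out any relapse still to come. Best/worst outcome can be so wide on a 0 to 136 scale that every result fails it. Complete case analysis and standard multiple imputation do not examine drop-out that depends on the unseen outcome.

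What is at stake is how the robustness of the 18-month result is read, not the main estimate. Agreement or disagreement with LOCF could reflect when and in which arm patients left rather than anything about treatment.

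**Working it through.** **Inputs from the protocol article.** Expected CAPS is 23.7 (SD 26.1) for TF-CBT and 34.8 (SD 25.7) for paroxetine, a difference of 11.1 (Sample size calculation). Attrition is 20%, with 45 per arm, and the requirement is "between 20 and 36 (depending on the actual ICC) patients per measurement per arm" (Sample size calculation adjustment). Minimum baseline is 45 (Participants). The CAPS range is 0 to 136 (Clinical assessments).

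**Assumptions not in the document.** A 10%/30% drop-out split, a mean baseline of 75, and a paroxetine relapse of 5 to 15 points. The expected means are used as the 18-month means of patients who stay.

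**The plan's own figures.** 36 / (1 - 0.20) = 45 per arm, as stated. Pooled SD = sqrt((26.1² + 25.7²)/2) = 25.9, and 12 / 25.9 = 0.463, matching the stated effect size of 0.46. At 20% attrition, 9 of 45 patients per arm are missing, leaving exactly the upper requirement of 36.

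**LOCF, all losses before T1.** With baseline B and drop-out dP (paroxetine) and dC (TF-CBT), the estimated difference is [(1 - dP) × 34.8 + dP × B] - [(1 - dC) × 23.7 + dC × B].

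- Equal 20%: B cancels, so 0.8 × 11.1 = 8.9.
- TF-CBT 30%, paroxetine 10%, B = 45: (31.32 + 4.5) - (16.59 + 13.5) = 5.7.
- TF-CBT 10%, paroxetine 30%, B = 45: (24.36 + 13.5) - (21.33 + 4.5) = 12.0.
- The same two splits at B = 75: -0.3 and 18.0.

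**LOCF, losses after T1, equal 20%.** If the arms differed by D at the last visit seen, the estimate is 0.8 × 11.1 + 0.2 × D. For D from 0 to 11.1 this runs from 8.9 to 11.1. So 8.9 is the largest dilution under equal drop-out, provided the last scores do not favour paroxetine. Put as relapse, the loss is at most 0.2 × (5 to 15) = 1 to 3 points. That maximum requires all the missing paroxetine patients to leave before any of their relapse is recorded.

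**Best/worst, read as opposite scale ends, 20% missing in each arm.**

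- Favourable to TF-CBT: (0.8 × 34.8 + 0.2 × 136) - 0.8 × 23.7 = 36.1.
- Unfavourable: 0.8 × 34.8 - (0.8 × 23.7 + 0.2 × 136) = -18.3.
- The unfavourable bound changes sign when missingness exceeds 11.1 / (136 + 11.1) = 7.5% per arm, or 3.4 of 45 patients.

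**Milder readings.** With a worst value of 60 to 100 instead of 136, the unfavourable bound is 8.9 - 0.2 × 60 = -3.1 to 8.9 - 0.2 × 100 = -11.1. With one common value in both arms and equal drop-out, the difference is 8.9 whatever that value is.

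**The case against.** The strongest reply is that these are two of four sensitivity approaches, that multiple imputation is on the same list, and that the section sets no rule by which a result failing LOCF or best/worst would be called fragile. That stands. A reader might infer that the long-term hypothesis is tested by LOCF and best/worst, or that they alone decide robustness. The document does not support this: the treatment difference is evaluated by the mixed model, with likelihood or multiple-imputation methods for missing data.

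A reader might also infer that LOCF removes relapse for everyone lost after T1. It does not. Someone lost after T2, T3 or T4 carries that visit's score, including relapse already recorded. Only relapse after the last visit is omitted, and if relapse is mainly in the paroxetine arm this works against the trial's own hypothesis.

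The larger LOCF figures need every loss to fall before T1, an unequal split, or a baseline of 75, none of which is in the document. The sample size section speaks of attrition at follow-up. Unequal early loss is still conceivable, because T1 comes after 24 weeks of paroxetine but after about 12 weekly TF-CBT sessions. The document also does not say whether LOCF may carry a T0 score; if it may not, patients lost before T1 simply leave that analysis.

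Finally, best/worst is not defined and might be meant for responder status. An article may leave that definition, and any further sensitivity analysis, to a fuller plan that is not shown, so the missing definition alone is no finding. What remains is that LOCF is named and fits the hypothesis poorly, and that none of the named methods is a plausible test of informative drop-out.

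**Conclusion.** The point holds as a minor to moderate weakness in the sensitivity analyses. The main analysis is not affected.

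Under equal 20% drop-out, LOCF dilutes an 11.1-point difference by at most 2.2 points, assuming the last scores do not favour paroxetine. Under an assumed 10%/30% split before T1 it can move the estimate either way, to 5.7 or 12.0 at the minimum baseline and further at higher baselines. Best/worst is uninformative at the planned attrition if it means opposite scale ends. It would be too strong to say that it cannot discriminate under any definition, since milder readings are narrower and the document does not choose one.

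**What to change.** Keep the likelihood-based mixed model on all randomised patients as the main analysis. Replace LOCF and scale-end best/worst as the sensitivity check with multiple imputation that adds arm-specific shifts to the imputed CAPS scores, for example 0 to 12 points worse in one or both arms. Report the shift at which the conclusion changes. For scale, a 12-point shift in the 20% missing from TF-CBT alone moves 11.1 to 11.1 - 0.2 × 12 = 8.7, so the grid should be extended if no change is reached within it. If LOCF is kept for comparison with older trials, label it descriptive and do not use it to judge robustness.

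The cost is a change of wording and modest programming, possibly outside the standard menus of the named SPSS version. Dropping LOCF loses some comparability with earlier trials.
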